### Ethical considerations

The study protocol was approved by the Valleywise Health Institutional Review Board (2019–060). On the consent, participants will be given as much time as needed to understand the purpose of study, required procedures, benefits and risks of their participation, and ask questions. Voluntary participation and anonymity will be emphasized. Participants will sign and date consent. They will also be asked to opt-in and sign a Social Media Etiquette Agreement for appropriate use of study social media accounts to interact as a community of mothers. Participants will be provided payment at the completion of study assessments associated with each home visit and phone calls between visits for the purposes of monthly check-ins and 24-h dietary recall. The total amount of money that can be earned for completing study-related tasks is $234. In addition to compensation, at each visit mothers and infants will also be given a “swag bag” of items of particular relevance to this population (e.g., diapers, wipes, custom-made baby milestone books, teethers, etc.). Additional incentives will be offered to participants which will include quarterly raffle prizes (small denomination gift cards and study-branded items) and incentives for friend referral ($5/friend for up to 5 friends; $25 total).

### Statistical analyses

To evaluate Aim 1, visit-to-visit changes in 24 h sleep and sleep-wake rhythmicity variables and their relationship to occurrence of RWG will be examined with a logistic TVEM. It can reveal critical periods during which changes in sleep-wake patterns accelerate/decelerate infant weight gain [114] and include other covariates with time-invariant effects. The TVEM model can be formulated as,

1$$ logit\;(RWG)={\beta}_0f(t)+{\Sigma}_v\kern0.5em {\beta}_vf(t)V+{\Sigma}_c\kern0.5em {\beta}_cC+\in $$where *f*(*t*) is a smooth function of time *t*, *V* is a set of variables with time-varying effects, *C* is a set of variables with time-invariant effects, *β*_0_, *β*_*v*_ and *β*_*c*_ are the corresponding coefficients, and *ϵ* is normally distributed random errors. We will impose no constraints on the *f*(*t*) function and the *β* coefficients except an assumption of smooth temporal progressions. To fit the model given the collected data, we will use the %TVEM SAS macro [115] and use a P-spline method to select the best-fitting model using knots (splitting points). Significance will be assessed based on the *p*-values of estimated *β* coefficients.

To evaluate Aim 2, we will apply the TVEM in model (1) with representing the alpha and beta diversity scores for each taxon. Because there are hundreds of taxa that may share dependencies, we will compute false discovery rates (FDRs) using the Benjamini–Hochberg procedure [116]. Taxa with FDR < 5% will be regarded as having significant associations. Given the hierarchical structure among taxa, we will further reduce the redundancies among significant taxa by ranking them on Akaike information criterion (AIC) values. Specifically, we will traverse the taxonomic tree (leaves to root) and compute AIC values for each clade. If a parent node has a lower AIC value than any of its child nodes, we will keep the parent node and remove the child nodes from the short-listed taxa.

To evaluate Aim 3, exploratory analysis will apply principal component analysis to examine if the combination of GM variables and sleep-wake variables can explain a higher variance of RWG than using each class of variables independently. Confirmatory analysis will use model (1) to include the main effects and pairwise interactions between GM diversity scores and sleep-wake variables. Significant p-values and positive coefficients of interaction terms will indicate synergistic effects. However, because there are potentially many GM taxa associated with RWG, model (1) may include too many variables and trivial effects that reduce the statistical power. In this case, we will take a nested approach to test synergies among correlated variables. Specifically, combining the significant variables identified in Aims 1 and 2, we will first test pairwise correlations. We will then group significantly correlated variables using Gaussian finite mixture models [117] that automatically determine the number of clusters. If GM diversity scores and sleep-wake patterns coexist in a cluster, we will use model (1) extended with interaction terms to test synergistic effects. For the proposed exfoliomic data, we will utilize systems biology approaches to illuminate transgenomic cross-talk between host exfoliated intestinal epithelial cells [84] and the genomes of the gut microbiota [83, 118] in a longitudinal cohort.

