**Methods:**

The Snuggle Bug/ Acurrucadito study is an observational, longitudinal study investigating whether 24-h, actigraphy-assessed, sleep-wake patterns and GM development are associated with RWG among infants in their first year. Based on the Ecological Model of Growth, we propose a novel conceptual framework to incorporate sleep-wake patterns and the GM as metabolic contributors for RWG in the context of maternal-infant interactions, and familial and socio-physical environments. In total, 192 mother-infant pairs will be recruited, and sleep-wake patterns and GM development assessed at 3 and 8 weeks, and 3, 6, 9, and 12 months postpartum. Covariates including maternal and child characteristics, family and environmental factors, feeding practices and dietary intake of infants and mothers, and stool-derived metabolome and exfoliome data will be assessed. The study will apply machine learning techniques combined with logistic time-varying effect models to capture infant growth and aid in elucidating the dynamic associations between study variables and RWG.

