## Background

### Early rapid weight gain in infancy contributes to childhood obesity

Early childhood obesity is a serious health problem. In 2019, 38.2 million U.S. children less than 5 years old were overweight or obese, with greater prevalence among low- and middle-income families [1]. Of those under 2 years, 8.1% had high weight-for-recumbent length (i.e., at or above the 95th percentile) [2]. Further, obese children are more likely to become obese adults [3]. Rapid weight gain (RWG) in the first 6 months of infancy, defined as a greater than 0.67 positive change in weight-for-age Z-score (difference between centile lines on standard growth charts) [4], is associated with greater total weight gain from 0 to 12 months and greater weight-for-length and weight-for-age percentiles at 36 months [5]. It also increases the odds of obesity across the life course [6–9] and relates to adverse health outcomes later in life, including hypertension, diabetes, and cardiovascular diseases [10]. Further, RWG in the first 3 months is more predictive of poor cardiometabolic outcomes than any other 3-month period in the first year of life [11]. Despite robust, globally diverse cohort data accounting for numerous confounding factors present from conception to birth on childhood obesity, few studies have focused on RWG determinants and timing in the birth-to-6-month period.

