### Aim and design

This study is designed as a five-year observational longitudinal study to investigate how 24-h sleep-wake patterns and GM influence RWG among infants in their first year. In this study, we aim to:
Investigate associations of infant sleep-wake patterns with subsequent RWG at 6 months and weight gain at 12 months using Time-Varying Effect Models (TVEM). We hypothesized that infants with suboptimal sleep-wake patterns (e.g., short sleep duration, poorer sleep quality [e.g., sleep percent, number of long awakenings], later bedtimes, and greater sleep-wake timing variability) will be more likely to experience RWG at 6 months and have greater total weight gain at 12 months than infants with optimal sleep-wake patterns.Investigate associations of GM development with RWG at 6 months and weight gain at 12 months. We hypothesized that infants with lower GM diversity, decreased relative abundance of beneficial microbes (e.g., *Bifidobacteria*), and increased pathogen abundance (e.g., *Staphylococcus*) across time will be more likely to experience RWG at 6 months and have greater total weight gain at 12 months.Evaluate whether temporal interactions exist between infant sleep-wake patterns and GM development, and if these relations influence RWG. We hypothesize that (1) infants with short sleep duration, poorer sleep quality, later bedtimes, and greater sleep-wake timing variability will exhibit lower GM diversity, decreased relative abundance of beneficial microbes, and increased pathogen abundance than infants with optimal sleep-wake patterns; and (2) infant sleep-wake patterns and GM development will have a synergistic effect on RWG, with suboptimal development of both factors increasing risk for RWG compared to either factor independently.

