### Assessment of RWG and infant growth

RWG is the primary outcome and weight gain over 12 months is a secondary outcome in this study. Infant length and weight will be measured with portable recumbent length boards (nearest mm) and electronic digital scales (nearest 0.1 kg), respectively. Infants will be nude at the time of weighing and will be measured recumbent to maintain measurement consistency. Weight measures will be recorded on the weight-for-age (W/A) percentile growth grid from the National Center for Health Statistics [65] to determine body mass in children under 2 years of age. W/A percentiles will be converted to Z-scores to allow group comparison by sex. Infant head circumference will be measured to the nearest mm using a flexible tape measure (Hopkins Medical Products) designed for infant heads. Infant waist circumference will be measured to the nearest mm using a Gulick II tape measure with tension spring.

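### Model (1) sets RWG, one yes/no value per infant fixed at 6 months, against visit-level predictors over time with no infant-level handling, so its p-values are invalid if it is fitted as printed

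*Protocol article*

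**What the plan says.** - **Outcome.** Assessment of RWG and infant growth: "RWG is the primary outcome and weight gain over 12 months is a secondary outcome in this study". The Background gives RWG in the first 6 months as "defined as a greater than 0.67 positive change in weight-for-age Z-score". Aim 1 is to "Investigate associations of infant sleep-wake patterns with subsequent RWG at 6 months". Each infant therefore has one value.
- **Exposures.** Per the abstract, sleep and gut microbiota are "assessed at 3 and 8 weeks, and 3, 6, 9, and 12 months postpartum". Two of the six visits come after the outcome is fixed.
- **Model.** Under Statistical analyses, the Aim 1 predictors are "visit-to-visit changes in 24 h sleep and sleep-wake rhythmicity variables", and the "sleep-wake rhythmicity variables and their relationship to occurrence of RWG will be examined with a logistic TVEM". Model (1) sets logit(RWG) equal to a time-varying intercept, time-varying effects of V, time-invariant effects of C, and a term that "is normally distributed random errors". It shows no infant index, random effect, working correlation or clustered variance. Significance is read from the p-values of the coefficients.
- **Reuse.** The same model serves Aim 2, with p-values passed to a Benjamini-Hochberg step at 5% FDR, and the confirmatory interaction tests of Aim 3.
- **Power.** Under Power analysis and target population, Aims 2 and 3 were simulated with a mixed-effects logistic model and six repeated measures per predictor.

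**The concern.** A model in visit time needs one row per infant per visit, but RWG has one value per infant. The only way to fill the rows is to copy that value. The time-varying intercept shows the mismatch, since the log-odds of an event defined once at 6 months do not evolve over visits.

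Nothing in the printed model accounts for the copying. If the rows are treated as separate observations, the standard errors do not reflect the number of outcomes actually observed. This affects the primary outcome and then spreads: the FDR step in Aim 2 needs valid p-values as input, and the nested approach in Aim 3 carries forward the variables found significant in Aims 1 and 2.

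An article may leave much to an analysis plan. Here, however, it prints the equation, the software and the test criterion, so the model is fixed as written.

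**Working it through.** **Inputs from the protocol.** Six visits, of which four are at or before 6 months (3 weeks, 8 weeks, 3 and 6 months); correlation 0.5 with compound symmetry (Aim 1 power statement); 160 infants (Aims 2-3, before attrition); alpha 0.05. **Assumed:** two-sided tests; correlation 0.3-0.7 as a range for the exposures; RWG share 50%, with 25% as a check.

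**The plan's own figures.** For a constant group difference of 1/3 SD over six time points, n per group = 2(1.96+0.84)² × [(1+5×0.5)/6] / (1/3)² = 2 × 7.849 × 0.5833 × 9 = 82.4, so 83 per group and 166 in total. With retention falling linearly from 1.0 to 0.8 this becomes 92.0 per group, total 184, as stated. The 192 is 160 × 1.2. That calculation treats RWG as a grouping of infants, one value each, and counts infants. Model (1) does not.

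**Step 1, constant effect by formula.** When one outcome is copied to m rows and the rows are treated as independent, the variance of the effect is understated by D = 1+(m−1)ρ. The true rejection rate of a nominal 5% test is 2[1−Φ(1.96/√D)].
- Level exposure, m=6, ρ=0.5: D=3.5, 1.96/1.871=1.048, rate 29.5%.
- Level exposure, m=4, ρ=0.5: D=2.5, 1.96/1.581=1.240, rate 21.5%.
- Time-invariant covariate (ρ=1): D=6 gives 42%; D=4 gives 33%.

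**Step 2, visit-to-visit changes by formula.** Under compound symmetry successive changes have correlation −0.5. The sum of k changes is last minus first, with variance 2σ²(1−ρ), against k × 2σ²(1−ρ) if they were independent. So D=1/k. With six visits (k=5), 1.96/√0.2=4.38 and the rate is about 0%. With four (k=3), 1.96/√(1/3)=3.39 and the rate is 0.07%. The test is conservative.

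**Step 3, null simulation for time-varying effects.** 160 infants, 1,000 runs per cell, each infant's RWG value copied to every row. Low-order polynomials stand in for the P-spline. Rejection rates of the naive nominal 5% joint test, ρ=0.5:

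| Predictor and effect shape | Six visits | Four visits |
|---|---|---|
| Level, constant | 30% | 22% |
| Level, linear in time | 22% | 15% |
| Level, quadratic in time | 16% | 11% |
| Level, separate effect per visit | 9% | 7% |
| Change, constant / linear / quadratic | 0 / 0 / 0.4% | 0.1 / 2.1 / 6.5% |
| Time-invariant covariate | 45% | 36% |

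For ρ from 0.3 to 0.7 the six-visit ranges are 23-35% (constant), 15-26% (linear) and 11-22% (quadratic). The four-visit ranges are 17-26%, 9-16% and 8-13%. With a separate effect per visit, each pointwise test stays at about 4-5%. An RWG share of 25% gives the same picture. Infant-clustered standard errors bring the rate to about 4-7% in every scenario.

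**Step 4, would a random intercept mend it?** No. With an outcome constant within infant, the likelihood keeps rising as the intercept variance grows, because a larger variance makes identical values within each infant more probable. The variance has no finite estimate.

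**The case against.** - **Independence is not stated.** A reader might infer that the plan assumes independent errors. The text says only that they are normal, and the power section used a mixed model, so the authors did think about dependence. The documents also do not say how the cited SAS macro computes variances. This stands: naive analysis is what results from following the printed equation, not something the authors declare. The mixed model would not help in any case (Step 4).
- **The direction can reverse.** A reader might conclude that all p-values are far too small. The documents do not support that. The predictors named for Aim 1 are changes between visits, for which the naive test can be conservative. That is still an invalid p-value, with loss of power in place of false positives. The Aim 1 hypotheses can also be read as levels, Aim 2 enters diversity scores, and the covariates C are not change scores, so inflation remains a risk there.
- **The largest figures are special cases.** About 30% for V, and standard errors understated 1.9-fold (√3.5), apply to a constant effect of a level exposure over six rows. A time-varying model is used for other shapes, where the rates are lower. Six rows is also an upper bound: four visits fall by 6 months, and change scores give at most five rows.
- **Shared f(t).** The equation could be read as forcing one time shape on every effect. The text after it says that f(t) and the coefficients are unconstrained apart from smoothness, so this is loose notation and not a modelling error.

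**Conclusion.** The point holds in a limited form. Model (1) does not fit the outcome it is given: RWG is one value per infant, the model is in visit time, nothing handles the repetition, and the normal error term is misplaced. Fitted as printed with the outcome copied across rows, it gives invalid p-values. At correlation 0.5 they are too small for smooth effects of level exposures (about 16-30% rejection at a nominal 5% with six visits, 11-22% with four) and for time-invariant covariates (about 36-45%). They can be too large for visit-to-visit changes, and pointwise tests with visit-specific effects are unaffected.

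These sizes rest on compound symmetry, two-sided tests, polynomials in place of the P-spline, and rows analysed without any clustering correction.

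A separate defect in the same model is that the eligible visits are not restricted. Exposures at 9 and 12 months could enter as predictors of an outcome already fixed at 6 months, although Aim 1 speaks of subsequent RWG.

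**What to change.** 1. For RWG at 6 months, admit only exposures measured before the outcome is fixed, and list the visits. Actigraphy is worn for the 5 days after each visit (Assessment of sleep), so the 6-month sleep recording follows the 6-month weighing and needs an explicit decision.
2. Choose one form and state what a row of data is:
   - one record per infant, logit P(RWG_i) = β0 + Σ_v Σ_t β_v(t)V_iv(t) + Σ_c β_c C_ic, with t over the eligible visits and β_v(t) smoothed across them; or
   - the time-varying effect model with infant-clustered standard errors (sandwich/GEE or infant-level bootstrap). Clustering alone does not replace item 1.
3. State whether V is a level or a change.
4. Delete the additive normal error and write a separate β_v(t) for each variable.
5. Apply the same to Aims 2 and 3, before the FDR step and before variables are selected for the interaction tests.

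The cost is modest programming and, in most cases, wider intervals. No new data are needed.

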## Discussion

Excess weight for infant age and childhood obesity remain highly prevalent with significant potential for negatively impacting growth, development, and health outcomes across the life course. Early infant RWG is a meaningful, early heralding risk factor for subsequent adiposity [119–121]. While prenatal exposures and feeding-related predictors of early infant RWG are known [122–125], they do not wholly explain the variance in accelerated weight gain. Less is known about other modifiable factors in early life that may be protective or detrimental. Suboptimal 24-h sleep-wake and commensal GM development and maturation are associated with subsequent adiposity in childhood and adulthood, yet their relationships with infant RWG are less known. In our Snuggle Bug/Acurrucadito Study, we aim to investigate sleep-wake and GM development across infancy in association with subsequent RWG independently, examine the temporal crosstalk between sleep-wake pattern and GM development, and explore whether these interactions affect RWG propensity. There are several noteworthy aspects in this protocol. The Snuggle Bug/Acurrucadito study will identify multidimensional factors that may contribute to the development of childhood obesity, especially among high-risk populations such as those with greater maternal BMI and racially and ethnically-diverse mothers of low-income. This study proposes a novel EMG theoretical framework to ensure a comprehensive understanding about the interacting socio-environmental, sleep, and infant GM influences on infant adiposity outcomes. We are employing a prospective longitudinal approach to assess multiple objective and self-reported parameters at clinically meaningful intervals throughout the first 12 months of life that will provide robust and accurate measures of sleep, GM, growth, and the maternal-infant, familial, and environmental context. The non-invasive longitudinal fecal analyses will allow us, for the first time, to identify critical molecular biomarkers that define the relationship between establishment of 24-h sleep-wake patterns, weight gain trajectories, early nutrition, the intestinal microbiota and intestinal gene expression. Our TVEM with frequent sampling approach in early infancy will capture the functional form of growth and aid in elucidating the dynamic associations between study variables and RWG. Further, to reduce language barriers and enhance our ability to recruit our target high risk population, all study measures to be collected will be translated by bicultural and bilingual staff, in either English or Spanish. All staff conducting home visits are able to communicate in English and Spanish. With these unique strengths, the study will provide a wealth of findings that will advance population and clinical-level approaches to childhood obesity prevention.

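### The only model written for Aims 1–3 takes RWG as a yes/no outcome; it cannot show the rate or shape of weight gain claimed for it, and a continuous Z analysis beside it would use information that the cut discards

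*Protocol article*

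**What the plan says.** All places are in the protocol article.

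- **Definition.** The Background describes RWG in the first 6 months as "defined as a greater than 0.67 positive change in weight-for-age Z-score".
- **Outcomes.** Under Assessment of RWG and infant growth: "RWG is the primary outcome and weight gain over 12 months is a secondary outcome in this study". The same section says that "W/A percentiles will be converted to Z-scores to allow group comparison by sex". Table 1 schedules infant weight and length at all six postpartum visits and lists birth weight in the birth history.
- **Model.** Under Statistical analyses, Aim 1 relates visit-to-visit sleep changes to RWG: "their relationship to occurrence of RWG will be examined with a logistic TVEM". Equation (1) has logit(RWG) on the left. Aim 2 applies the same equation to microbiota measures. The confirmatory part of Aim 3 applies it with interaction terms. No other outcome model is written.
- **Claims for the model.** Statistical analyses: "It can reveal critical periods during which changes in sleep-wake patterns accelerate/decelerate infant weight gain". Discussion: "Our TVEM with frequent sampling approach in early infancy will capture the functional form of growth".
- **Continuous outcome.** Aim and design names weight gain at 12 months beside RWG in Aims 1 and 2, and places it under TVEM in Aim 1.

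**The concern.** Two things do not fit together.

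First, the outcome in equation (1) is a threshold crossing. An infant whose Z rises by 0.70 counts the same as one whose Z rises by 2.0, and an infant at 0.65 counts the same as one at −1.0. A coefficient from such a model is a log odds ratio for crossing the line. The article nevertheless credits the model with findings about the speed and shape of growth. If results are reported as planned, readers could take an age-specific odds ratio for RWG as evidence that weight gain sped up or slowed down at that age.

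Second, the study is modest in size and will already hold the Z-scores. Reducing them to one binary label discards information on the outcome, so a real association with sleep or microbiota is more likely to be missed than in an analysis of the full scale.

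**Working it through.** **1. What equation (1) can and cannot estimate.** The time-varying coefficients multiply the predictors. They can show that sleep at one age is more strongly related to the odds of RWG than sleep at another. That is a legitimate sense of a critical period. The outcome, as defined in the Background, is one label per infant for the first 6 months. No coefficient in the equation is on the scale of Z per unit time, and no fitted curve is a growth curve. Rate and functional form would need a model whose outcome is weight-for-age Z at each visit.

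**2. The plan's own sample sizes** (Power analysis and target population).

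- *Aim 1, total 184.* Inputs: 6 time points, correlation 0.5, compound symmetry, 1/3 SD, α 0.05, power 0.8, 20% attrition. With a constant group difference and a two-sided test, n per group = 2(1.96 + 0.84)² × [(1 + 5 × 0.5)/6] / (1/3)² = 82.4, so 83 per group and 166 in total. Weighting each visit by the inverse square root of a retention that falls linearly to 80% gives 92 per group, or 184. This calculation compares RWG groups on a repeated measure; it is not a logistic model.
- *Aims 2–3, 160 and 192.* The 160 comes from a simulated mixed-effects logistic regression. It cannot be rebuilt because the RWG rate and random-effect variance are not given. The recruitment figure follows as 160 × 1.2 = 192.

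**3. Power with and without the cut.** This is a simplified check, not the planned TVEM: one predictor (the sleep average per infant), unadjusted, two-sided α 0.05, Z change and sleep jointly normal.

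- Retained infants: 192 × 0.8 ≈ 154.
- SD of a six-visit average: √[(1 + 5 × 0.5)/6] = 0.764.
- Standardised difference: d = 0.333/0.764 = 0.436.
- Correlation that gives this d when a share p of infants has RWG: r = d·p(1 − p)/φ(z_p).
- Continuous power ≈ Φ(atanh(r)·√151 − 1.96). Binary power ≈ Φ(d·√[154·p(1 − p)] − 1.96).

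| RWG share p | r | Continuous, formula | Binary, formula | Continuous, simulated | Logistic, simulated |
|---|---|---|---|---|---|
| 50% (implied by equal groups) | 0.273 | 93% | 77% | 94% | 79% |
| 40% (assumed) | 0.271 | 93% | 76% | 94% | 77% |
| 30% (assumed) | 0.264 | 91% | 70% | 92% | 72% |
| 20% (assumed) | 0.249 | 88% | 58% | 89% | 57% |

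The simulated columns use 1,500 datasets per cell. Repeat runs moved individual cells by up to about 2 points. Taken together they put the 50% case at about 78% against 94%, and the gap at 20% at about 30 points.

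**4. Sensitivity.**

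- *Visits used.* The 9- and 12-month visits fall after the 6-month outcome. With only the four visits up to 6 months, d = 0.333/√[(1 + 3 × 0.5)/4] = 0.422. The formulas then give 91% against 74% at 50% RWG, and 86% against 55% at 20%. The gap barely changes.
- *Reference point.* The relative efficiency of the cut is φ(z_p)²/[p(1 − p)]: 0.64 at 50%, 0.58 at 30% and 0.49 at 20%. If the logistic analysis is taken to have exactly 80% power, as stated for Aims 2–3, the continuous analysis would have 94%, 96% and 98%. The points gained are then 14, 16 and 18.

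**The case against.** Several stronger readings are tempting, and the article does not support them.

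- *That growth enters the study only as yes/no.* Weight gain over 12 months is a declared secondary outcome and is placed under TVEM in Aim 1. A journal article may leave a secondary model to the full plan, so its absence is not a fault in itself. What stands is that a 12-month gain does not isolate the 0–6 month window in which RWG is defined, and that the growth-rate claim in Statistical analyses is made for the logistic model.
- *That RWG is the wrong primary outcome.* It was chosen deliberately, the Background ties it to later obesity and cardiometabolic risk, and the aims ask who experiences it. Replacing it as the main test would change the question. That is a trade-off, not a correction.
- *That the study is underpowered because of the cut.* At the 50% share implied by equal groups, logistic power in the simplified check is about 78%, close to the 80% target. For Aims 2–3 the stated 80% already carries the cost of the cut. The larger gaps rest on RWG shares that the article does not give.
- *That the model says nothing about timing.* It does, through the repeated predictors.

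The simplified check also favours the continuous model through joint normality and linearity, so its figures are illustrative.

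**Conclusion.** The point holds in a limited form. The two statements about accelerated or decelerated gain and the functional form of growth go beyond what logit(RWG) can deliver. That conclusion needs no power assumption.

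The efficiency forgone is about 16 points at a 50% RWG share and about 30 points at an assumed 20% share. It rests on joint normality, a 1/3 SD difference, correlation 0.5, 154 retained infants and an unadjusted single-predictor model. It is a missed gain, not a failure to reach the stated power. A supporting continuous analysis is therefore a cheap improvement and does not require redesign.

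**What to change.** 1. Keep RWG, a Z change above 0.67, as the primary outcome and report it as planned.
2. Pre-specify, as a key supporting analysis for Aims 1–3, a linear model of the 0–6 month change in weight-for-age Z. Use one value per infant and the same predictors and covariates. Fix its place in the order of analyses in advance, so that it does not become an uncontrolled extra test.
3. Rest any statement on accelerated or decelerated gain, or on the functional form of growth, on an identity-link TVEM of visit-level weight-for-age Z that allows for within-infant correlation. Otherwise withdraw those statements from Statistical analyses and the Discussion.

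The cost is some plan wording and one further set of model runs, with no new visits, data or participants. The drawback is that a mean difference in Z is less directly clinical than an odds ratio for RWG, which is why RWG stays in the lead.
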